#### Statistical analysis

Primary Outcome: The primary analysis will compare the treatment groups on the 24-week HbA1c for the pre-pregnant cohort and on the 34-week HbA1c for the pregnant cohort, controlling for baseline HbA1c in an analysis of covariance that includes the treatment modality (pump/MDI) and strata used in randomization as covariates. We will obtain point and interval estimates of the treatment effect (the mean adjusted difference in follow-up HbA1c between treated and control groups) and also test the null hypothesis that the treatment effect is zero. The primary analysis will follow the intention-to-treat principle with all participants analyzed in the group to which they were randomized, regardless of actual sensor wear. In the analysis of the pre-pregnant cohort, in women who become pregnant before 24 weeks, the final outcome will be a measurement of HbA1c taken post-confirmation of pregnancy. In the analysis of the pregnant cohort, in women who do not reach 34 weeks gestation, the last HbA1c taken prior to 34-weeks will be used for the primary outcome. If important covariates remain imbalanced between treatment groups despite the stratified randomization, these covariates will be added to the regression model and the difference between adjusted and unadjusted estimates will be examined to assess the impact of this imbalance. Multiple imputation using earlier HbA1c measurements will be used to deal with HbA1c values that are missing at the final assessment.

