### Run-in

The participant wears a masked CGM for 6 days. This provides a baseline assessment of glycemic control and allows participants to wear the CGM before making a decision about whether or not to continue to be randomized. The participant must test using the HGM at least 4 times per day and wear the CGM for at least 5 days, obtaining at least 96 h of glucose values and have at least 24 h of values between 23.00–07.00 h to qualify for randomization. The run-in CGM data are downloaded for evaluation by an independent data coordinating center (Jaeb Center For Health Research Inc, Tampa, Florida, USA) and not reviewed by participants or their clinicians. Should the first run-in be unsuccessful (due to insufficient CGM data), a repeat CGM can be obtained.

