#### Sample size estimation

The trial will include 324 participants, with 110 in the pre-pregnant cohort (women planning pregnancy), and 214 in the pregnant cohort.

In both cohorts, the sample size is based on a clinically relevant difference in HbA1c of 0.5 %. For pregnant women, a cross-sectional standard deviation (SD) of 1.1 was used, as it is towards the upper limit of published HbA1c SD values ([9–11]. In pre-pregnant women, a SD value of 0.8 was used, based on reported SD values in a trial of CGM in young adults [12]. As this latter study also reported the SD of change over 26 weeks, it was possible to compute the correlation between repeated measurements. In the various study groups, these correlations ranged from 0.4 to 0.7. To be conservative, we used the lower value of 0.4 in our sample size calculations. In both cohorts (pre-pregnant and pregnant), sample size was computed for an analysis of covariance with the final HbA1c as the outcome and baseline HbA1c and treatment group as predictors. Power was set at 90 % and the two-tailed significance level was set at 5 %.

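### The primary ANCOVA is valid but makes no prespecified use of the masked run-in CGM that every randomized woman has; adding one CGM summary is a low-cost option whose gain is uncertain

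*Protocol article*

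**What the plan says.** The Statistical analysis section of the protocol article compares final HbA1c between arms, "controlling for baseline HbA1c in an analysis of covariance that includes the treatment modality (pump/MDI) and strata used in randomization as covariates". Under Randomization, the strata are insulin delivery (pump or MDI) and baseline HbA1c split at one cut-point per cohort. The stratum therefore repeats, in coarser form, the HbA1c value already in the model. No CGM variable is named. Other covariates come in only if they are judged important and turn out to be imbalanced between arms.

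Under Run-in, a woman qualifies for randomization only with at least 96 h of masked CGM values, at least 24 h of them overnight. Overall study design names a single masked device for this phase. The recordings go to an independent data center and are not reviewed by participants or their clinicians. Of the masked wear the article says: "This provides a baseline assessment of glycemic control". Baseline CGM time in target also appears among the secondary outcomes of both cohorts.

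Sample size estimation uses an ANCOVA with baseline HbA1c and treatment group as the only predictors. Of the baseline-to-final correlation, reported there as 0.4 to 0.7, it says: "To be conservative, we used the lower value of 0.4 in our sample size calculations".

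**The concern.** A covariate measured before allocation improves the precision of a treatment contrast to the extent that it predicts the outcome beyond what is already in the model. The run-in CGM is a natural candidate. It is recorded before allocation with one specified device, is essentially complete because of the entry rule, and is described by the article as a measure of baseline glycemic control. At the planning correlation of 0.4, baseline HbA1c explains 0.4² = 16 % of the variance of final HbA1c and leaves 84 %, so there is room for a second predictor.

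The imbalance rule does not fill this gap. A prognostic covariate helps precision whether or not it happens to be imbalanced, and a rule triggered by observed imbalance is not a prespecified precision adjustment. At stake is the width of the interval for the HbA1c difference, and a little power. Bias is not at issue.

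**Working it through.** **Inputs from the article**

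- Significance level: "the two-tailed significance level was set at 5" per cent. Power: "Power was set at 90" per cent.
- Difference, both cohorts: "the sample size is based on a clinically relevant difference in HbA1c of 0.5" (HbA1c percentage units).
- SD, pregnant: "a cross-sectional standard deviation (SD) of 1.1 was used". SD, pre-pregnant: "a SD value of 0.8 was used".
- Baseline-to-final correlation ρ = 0.4, from a stated range of 0.4 to 0.7.
- Attrition 20 % (pregnant) and 15 % (pre-pregnant), from the Abstract. Allocation 1:1. Planned N 214 and 110.

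**Input not in the article**

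- r, the partial correlation of a run-in CGM summary with final HbA1c given baseline HbA1c. Assumed, 0 to 0.4.

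**Step 1: reproduce the planned size.** Residual SD = SD × √(1 − ρ²). Per arm, n = 2 × [residual SD × (1.960 + 1.282) / 0.5]².

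- Pregnant: 1.1 × √0.84 = 1.008; n = 85.4, so 86 per arm; 172 / 0.80 = 215 (213.6 without rounding up). Stated: 214.
- Pre-pregnant: 0.8 × √0.84 = 0.733; n = 45.2, so 46 per arm; 92 / 0.85 gives 109, or 110 if each arm is inflated and rounded separately. Stated: 110.

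Both planned figures reproduce.

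**Step 2: power of the model as planned.** Evaluable women per arm: 214 × 0.80 / 2 = 85.6 and 110 × 0.85 / 2 = 46.75. SE = residual SD × √(2/n); power = Φ(0.5/SE − 1.960).

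- Pregnant: SE = 1.008 × √(2/85.6) = 0.154; power 90.1 %.
- Pre-pregnant: SE = 0.733 × √(2/46.75) = 0.152; power 90.9 %.

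**Step 3: add one CGM covariate.** Residual variance is multiplied by (1 − r²), so the interval narrows by 1 − √(1 − r²). With ρ = 0.4:

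| Assumed r | Variance removed | Interval narrower by | Power, pregnant | Power, pre-pregnant |
|---|---|---|---|---|
| 0 | 0 % | 0 % | 90.1 % | 90.9 % |
| 0.1 | 1 % | 0.5 % | 90.3 % | 91.2 % |
| 0.2 | 4 % | 2.0 % | 91.2 % | 92.0 % |
| 0.3 | 9 % | 4.6 % | 92.5 % | 93.3 % |
| 0.4 | 16 % | 8.4 % | 94.3 % | 94.9 % |

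**Step 4: how far r can move.** r = (r_cf − ρ × r_cb) / √[(1 − ρ²)(1 − r_cb²)], where r_cb is the correlation of CGM with baseline HbA1c and r_cf that of CGM with final HbA1c. Both are assumed.

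- ρ = 0.4, r_cb = 0.6, r_cf = 0.5: r = (0.5 − 0.24) / √(0.84 × 0.64) = 0.355, which removes 12.6 % of the residual variance.
- ρ = 0.7, r_cb = 0.7, r_cf = 0.5: r = (0.5 − 0.49) / √(0.51 × 0.51) = 0.02, which removes almost nothing.

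**Step 5: the upper end of the stated correlation range.** With ρ = 0.7 and no CGM covariate:

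- Pregnant: residual SD = 1.1 × √0.51 = 0.786; SE = 0.786 × √(2/85.6) = 0.120; power 98.6 %.
- Pre-pregnant: residual SD = 0.8 × √0.51 = 0.571; SE = 0.571 × √(2/46.75) = 0.118; power 98.8 %.

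For a given r the interval still narrows by the percentage in the table, but little power is left to gain.

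**The case against.** The strongest case against raising this is that nothing in the plan is wrong. The ANCOVA adjusts for the baseline of the outcome and for the stratification factors, is fixed in advance, and has at its core the model used for the sample size. That one more covariate might help can be said of almost any trial, and an analysis plan that is not shown may already include it. This stands, and it keeps the point at the level of a suggestion.

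The benefit is also assumed. The article gives no correlation between run-in CGM and later HbA1c. Six days of glucose and a baseline HbA1c measure related things at about the same time, so r could be close to zero. The 84 % of variance left over belongs to a correlation chosen as conservative, and the pregnant SD is likewise described as towards the top of published values. This stands too, which is why the range starts at 0 and the upper correlation is shown.

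A reader might infer that the trial discards a known amount of precision, or that its primary analysis is deficient or underpowered. The article supports neither reading: the size of the gain cannot be derived from it, and planned power is met without CGM.

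What survives is narrower. The covariate set is stated, a second glycemic baseline exists for every randomized woman, and the imbalance rule does not put it to use for precision.

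**Conclusion.** The point holds as an efficiency improvement of low severity, to be considered and not required. The planned primary ANCOVA is valid and consistent with the sample size. Adding one run-in CGM summary would bring a gain between negligible and moderate: for r from 0 to 0.4, an interval narrower by 0 to about 8.4 %, and power higher by 0 to about 4.2 points in the pregnant cohort (94.3 − 90.1) and 4.0 points in the pre-pregnant cohort (94.9 − 90.9).

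These figures rest on the planning SDs, on attrition read as the fraction not analysed, on ρ = 0.4, and on an r that is assumed throughout. The stated correlation range comes from the young-adult trial that also supplied the pre-pregnant SD, so its use for pregnant women is itself an assumption. If ρ is nearer 0.7, power is already well above 90 % and the gain in power is smaller.

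**What to change.** Before unblinded data are seen, prespecify one continuous summary of the run-in CGM, for example mean glucose from the qualifying run-in, as a covariate in the primary ANCOVA of both cohorts. State which recording counts when the run-in was repeated. Do not leave its entry to the imbalance rule.

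In the pregnant cohort, gestational age at randomization may be added as well. Entry is allowed up to 13 weeks 6 days and the outcome is set at 34 weeks, so the time between the two varies between women. The article gives no basis for quantifying that gain.

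The cost is one or two degrees of freedom and a linkage of run-in data from the CGM data center to the HbA1c data held by the trial's coordinating center. No new data collection and no change to the sample size are needed.

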#### Sample size estimation

The trial will include 324 participants, with 110 in the pre-pregnant cohort (women planning pregnancy), and 214 in the pregnant cohort.

In both cohorts, the sample size is based on a clinically relevant difference in HbA1c of 0.5 %. For pregnant women, a cross-sectional standard deviation (SD) of 1.1 was used, as it is towards the upper limit of published HbA1c SD values ([9–11]. In pre-pregnant women, a SD value of 0.8 was used, based on reported SD values in a trial of CGM in young adults [12]. As this latter study also reported the SD of change over 26 weeks, it was possible to compute the correlation between repeated measurements. In the various study groups, these correlations ranged from 0.4 to 0.7. To be conservative, we used the lower value of 0.4 in our sample size calculations. In both cohorts (pre-pregnant and pregnant), sample size was computed for an analysis of covariance with the final HbA1c as the outcome and baseline HbA1c and treatment group as predictors. Power was set at 90 % and the two-tailed significance level was set at 5 %.

#### Data management

The continuous glucose monitoring data management and analyses will be handled by the Jaeb Center for Health Research, Tampa, Florida. All other data and statistical aspects will be handled by the Clinical Trials Services/Centre for Mother, Infant and Child Research, Toronto, Ontario, and the trial statistician.

#### Trial steering committee

A trial steering committee will be responsible for the conduct of the trial. They will meet by teleconference on a quarterly basis to review the progress of the trial or on an ad hoc basis should the need arise.

#### Safety considerations

A Data Safety Monitoring Board (DSMB) will be established and will include experts in or representatives of the fields of endocrinology, obstetrics, epidemiology, and clinical trials methodology. They will meet after the initial safety analysis is completed, which will be done after 50 % of the pregnant group has been recruited. Serious unanticipated adverse events will be reported to the DSMB should the need arise.

## Discussion

### Implications of the findings

We aim to evaluate the impact of RT- CGM on glycemic control in two groups of women, those who are planning pregnancy and women in early pregnancy. If we find an improvement, the use of the RT-CGM will be encouraged and potentially reimbursed. We may also be able to determine if RT-CGM is more helpful in certain subsets of participants (e.g. those using pump or MDI), and whether the use of RT-CGM will affect maternal and neonatal outcomes. If we do not find that RT-CGM is beneficial, then other technologies such as closed-loop insulin delivery, may be indicated to facilitate optimal glycemic control in type 1 diabetes pregnancies.

### Dissemination

A report will be written for the funding bodies and for peer-reviewed publication and will be disseminated to international lay and scientific audiences.

## Conclusion

Results from studies in non-pregnant populations suggest that CGM improves glycemic control. Results from two randomized studies performed during pregnancy are conflicting, one with and one without improved glycemic control. This is the first study to look at continuous use of RT- CGM both in women planning pregnancy and in women during early pregnancy. It will inform patients, caregivers, and funding agencies regarding the use of CGM in the pregnant woman with type 1 diabetes.

## Abbreviations

AUC, Area under the curve; DSMB, Data Safety Monitoring Board; HbA1c, Glycated haemoglobin; HGM, Home glucose monitoring; MDI, Multiple daily injections; RT-CGM, Real-time Continuous glucose monitoring; SD, Standard deviation
